### Standard prenatal care

2.4

All the women will receive their routine prenatal care which includes daily doses of ferrous gluconate (300 mg, equivalent to 60 mg of elemental iron) and folic acid (5 mg), and 4-weekly doses of malarial chemoprophylaxis in the form of Sulfadoxine-Pyrimethamine (SP) tablets (from enrolment to 36 weeks of gestation) or instead daily doses of Cotrimoxazole 980 mg for women with CD4 + cell counts < 200 cells/mm^3^ according to established protocol for *Pneumocystis carinii* prophylaxis^[20]^ irrespective of treatment assignments. Alternatively, daily proguanil tablet (100 mg) is given to women with known or recent allergy to Sulphonamides from enrolment to delivery. All women will also be commenced on ART at some point during their follow-up according to the National HIV prevention and treatment guidelines.^[21]^

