### Confirmatory outcome variables

2.6

Primary endpoints – Preterm birth (delivery before 37 completed weeks of pregnancy) and low birth weight in term neonates (baby's birth weight less than 2.5 kg).

Secondary endpoints – HIV disease progression (change in CD4 + cells count, viral load and stage of the disease); mid-trimester miscarriage, change in haemoglobin levels; adverse events (AE) such as hepatotoxicity, gastrointestinal disturbances, dermatologic effects (nail and hair loss and dermatitis), and neurotoxicity; and perinatal mortality (number of stillbirths and neonatal deaths in the first week of life).

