#### Sample size

2.7.1

Using the data from our previous study,^[11]^ we propose to enrol 148 participants in the study to investigate the effect of selenium supplementation on the primary endpoints. The study is powered for a 2-sided test with a Type I error rate of 5% and 95% power, that is, Z_α_ = 1.96 and Z_β_ = 1.64, adjusted for a 20% drop-out rate. We also propose to enrol 180 participants to detect an effect size of 0.3 of selenium supplementation on the major secondary endpoint (reduction in HIV disease progression). This is powered for a 2-sided test with a Type I error rate of 5% and 80% power, that is, Z_α_ = 1.96 and Z_β_ = 1.64, adjusted for a 20% drop-out rate. Therefore, a total sample size of 180 is used in this study with 90 HIV-infected women randomised into each of the trial arms to assess the effects of selenium supplementation on the primary and secondary outcome variables.

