### Statistical analyses

2.8

The intention-to-treat principle will be used in the final analyses. Statistical analyses will be carried out using SPSS version 23.0 for Windows (Armonk, NY: IBM Corp.). The associations between any 2 groups of continuous variables will be tested using the independent sample or paired *t* test (normal distribution) or the Mann-Whitney *U* test (skewed data) and that of 2 groups of categorical variables with chi-square or Fishers exact test where appropriate. A series of multivariable analyses using binary logistic regression model will also be carried out to identify and control for several possible confounders of the primary and secondary outcome variables. Statistical significance will be defined as *P* < .05.

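### The endpoint that sets N = 180, HIV disease progression, is three variables with no deciding one and no stated effect-size metric, and paired tests are not restricted to description

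*Protocol article*

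**What the plan says.** - **Protocol article, 2.7.1 (Sample size).** The primary endpoints need 148 women. The trial enrols 180, a figure based on an "effect size of 0.3 of selenium supplementation on the major secondary endpoint (reduction in HIV disease progression". The settings are "a 2-sided test with a Type I error rate of 5% and 80% power, that is, Z_α_ = 1.96 and Z_β_ = 1.64". An allowance of 20% for drop-out is then made. The 180 are split 90 per arm. The variable and the metric of the 0.3 are not named.
- **2.6 (Confirmatory outcome variables).** The endpoint is "HIV disease progression (change in CD4 + cells count, viral load and stage of the disease". No composite, order or lead variable is given.
- **2.8 (Statistical analyses).** The sentence on tests begins: "The associations between any 2 groups of continuous variables will be tested using the independent sample or paired". It is the t test that is meant, and the Mann-Whitney test is listed for skewed data, chi-square or Fisher's exact test for categories, and logistic models for adjustment. P < .05 is the only threshold. The principle is intention-to-treat. No test or contrast is tied to progression.
- **2.4 (Standard prenatal care).** "All women will also be commenced on ART at some point during their follow-up".
- **2.5.1 (Data collection and management).** CD4 count, viral load and WHO stage are recorded at enrolment and again at delivery, so each woman has a before-after pair.

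**The concern.** The sample-size section treats progression as one quantity with one effect, while the endpoint section makes it two laboratory measures and an ordered clinical stage. The 0.3 cannot be traced to any one of them. A reader of the results could not tell which finding would count as reduced progression: CD4, viral load, stage, any of them or all of them. Because each can be tested at P < .05, the chance of a nominally positive progression result exceeds that of a single test.

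The listed paired test adds a second ambiguity. For a change endpoint it would compare enrolment with delivery inside one arm. Since ART is to be given to all women, CD4 and viral load can move in both arms whether or not selenium does anything, so such a change is not evidence for selenium.

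Progression is half of the stated aim (Introduction) and half of what the Discussion proposes to draw on. It is also the endpoint that moved the trial from 148 to 180.

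**Working it through.** **Inputs.** From 2.7.1: effect size 0.3, two-sided 5%, Z values 1.96 and 1.64, 20% drop-out, 180 enrolled, 90 per arm. Evaluable per arm: 90 × 0.8 = 72. Assumptions, because the documents give no figures: the correlation between the three test statistics (0 to 0.8), and the test statistics taken as jointly normal.

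**1. The plan's own figure.** (1.96 + 1.64)² / 0.3² = 12.96 / 0.09 = 144, and 144 / 0.8 = 180. The figure is reproduced exactly, but only with Z_β = 1.64. That is the value for 95% power, whereas the text says 80% (Z_β = 0.84). With 0.84 the same formula gives 2.80² / 0.09 = 87.1, or 108.9 after drop-out.

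**2. What metric does 180 imply?** The same arithmetic fits three readings:
- a one-sample or paired standardised change of 0.3;
- a 1-df chi-square comparison with w = 0.3, where total N is 12.96 / 0.3² = 144;
- a two-arm standardised difference of d = 0.6, where total N is 4 × 12.96 / 0.6² = 144.

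It does not fit a two-arm difference of d = 0.3. At 80% power that needs 2 × (1.96 + 0.84)² / 0.3² ≈ 175 per arm, 350 evaluable, and 350 / 0.8 ≈ 438 enrolled. So N identifies neither the variable nor the contrast.

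**3. Three between-arm tests at 5% with no selenium effect** (trivariate normal simulation, equal correlation):

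| Correlation | At least one P < .05 | At least one P < .05 favouring selenium |
|---|---|---|
| 0 | 14.3% | 7.3% |
| 0.3 | 13.6% | 6.8% |
| 0.5 | 12.5% | 6.2% |
| 0.7 | 10.9% | 5.4% |
| 0.8 | 9.9% | 4.9% |

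At correlation 0 this is 1 − 0.95³ = 14.3%. For a single test the two columns would read 5% and 2.5%.

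**4. Power if 0.3 is a between-arm standardised difference.** The expected z is 0.3 × √(72/2) = 1.8. Power is Φ(1.8 − 1.96) ≈ 44% by the normal approximation and 43% by the t distribution, without baseline adjustment. The difference detectable with 80% power is (1.96 + 0.84) × √(2/72) ≈ 0.47.

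**5. Within-arm test, for illustration.** Suppose both arms share the same standardised change and selenium does nothing. A paired test in the selenium arm (72 women) is significant in about 39% of trials for a change of 0.2 SD, 71% for 0.3 and 99% for 0.5. It is significant with selenium but not with placebo in 24%, 21% and 1% respectively. The sizes of change are assumptions.

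**The case against.** **The design already implies the contrast.** The trial is randomised, placebo-controlled and analysed by intention-to-treat, and 2.7.1 speaks of an "effect size of 0.3 of selenium supplementation". The paired test appears once, in a generic list. This stands. A reader might infer that within-arm testing is planned as the decisive analysis, or that no between-arm comparison is intended. The documents do not support either, and the exact match of 180 to a paired formula does not prove it, because w = 0.3 and d = 0.6 give the same number. What remains is that no sentence confines paired tests to description.

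**Allocation of tests to secondary endpoints belongs in an analysis plan.** Largely true. The variable and metric behind N are different: the sample-size section states them, but in a form that matches no single variable in 2.6.

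**An effect size of 0.3 is meaningless for clinical stage.** This is another tempting inference, and it does not hold. The text does not say that 0.3 is a standardised mean difference, and w = 0.3 would suit a two-category comparison. The metric is unstated, not shown to be wrong.

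**The magnitudes depend on assumptions.** This also stands. The 10% to 14% counts results in either direction; the share favouring selenium is about half. If selenium truly worked equally on all three variables, the tests would disagree in about 49% of trials at d = 0.3 and correlation 0.5, but in only about 11% at d = 0.6, a metric that reproduces 180. No weight is put on that figure. The within-arm percentages rest on ART-driven changes that the documents do not quantify. Section 2.5.1 records duration of ART use at enrolment, so some women may already be on treatment and change little.

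**Conclusion.** The point holds in a limited form and should be fixed. The endpoint that sets N = 180 has three component variables, no deciding one and no effect-size metric. Followed as written, it gives about a 10% to 14% chance of at least one significant between-arm result with no selenium effect. In selenium's favour the chance is about 5% to 7%, against 2.5% for one test. These figures assume three tests at two-sided 5% with correlations from 0 to 0.8.

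A before-after change in the selenium arm would not be evidence for selenium. The protocol does not say that it would be used that way; it only leaves the paired test unrestricted.

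The stated 80% power cannot be carried over to a between-arm standardised difference of 0.3, where power is about 43% to 44% with 72 evaluable women per arm.

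**What to change.** Before unblinding:

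- **2.6 and 2.7.1:** name one variable as deciding for HIV disease progression, either CD4 count or log10 viral load, at the sponsor's choice. Define the contrast as the selenium-versus-placebo difference at delivery, adjusted for the enrolment value already collected. Report the other two variables as supportive, with estimates and confidence intervals and no separate claim of reduced progression.
- **2.7.1:** state what kind of effect size 0.3 is, correct the mismatch between 80% power and Z_β = 1.64, and restate the power or detectable effect to match. Without baseline adjustment and with 72 evaluable per arm, either quote about 43% to 44% power for a standardised difference of 0.3, or a detectable difference of about 0.47 at 80% power. Keeping both 0.3 and 80% for this contrast would need about 438 enrolled. Any gain from baseline adjustment depends on the enrolment-to-delivery correlation, which the protocol does not give and which would have to be stated as an assumption.
- **2.8:** state that paired within-arm tests are descriptive and that any statement about selenium rests on the between-arm comparison.

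**Cost.** No new measurements are needed, and no more women if the sponsor accepts the restated power. There are two downsides. A positive result on only one of the supportive variables can no longer be claimed as reduced progression. The stated power or detectable effect also becomes less favourable.

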#### Data collection and management

2.5.1

At enrolment, the investigators will collect data on the participants’ socioeconomic status, education, and obstetric history, duration of HIV diagnosis (in months), WHO clinical stage of the disease,^[22]^ type and duration of ART use (in months), baseline Haemoglobin (Hb) levels (in g/dL), CD4 + cells count (in cells/mm^3^) and viral load (in copies/mL), and BMI (actual maternal weight is calculated by subtracting the estimated fetal weight at enrolment using a normogram chart from the measured maternal weight) (in kg/m^2^) using a structured interviewer-administered questionnaire. Gestational age is based on the date of the participant's last menstrual period, which will be obtained at the time of random assignment. Data collection begins on the day a participant is allocated into an intervention arm and continues until the termination of the trial or until the participant withdraws from the trial at any time for any reason. At delivery, data will be collected from the participants’ case notes on the latest CD4 + cells count and viral load (done within the last 6 weeks of delivery), WHO stage of the disease, and latest Hb levels. The total duration of supplement intake – selenium or placebo (in weeks), level of compliance to use of the supplement (good compliance level is defined as usage of at least 10 of the 16, 2-weekly prescribed tablets), mode of delivery, gestational age at delivery (in weeks) and the baby's birth weight (in grams) will also be recorded in the questionnaire. Original data will be transferred to an electronic database system located in a guarded facility at the trial site by the research assistant. Access to the study data is restricted. The PI will have the access to the final dataset. An independent steering committee will monitor and examine strict compliance with the study protocol (Fig. 1 and Table 1). Trial progression or protocol modification will be updated in the registered database (Pan African Clinical Trial Registry, PACTR) and reported to the LUTH's ethical committee that will provide the oversight functions of data and safety monitoring in the course of the study.

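### The protocol gives no analysis scale for viral-load change other than copies/mL; read literally it tests raw differences, which Mann-Whitney does not repair and which can hide a real effect if many women start ART on study

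*Protocol article*

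**What the plan says.** - *Confirmatory outcome variables (2.6)* lists, among the secondary endpoints, "HIV disease progression (change in CD4 + cells count, viral load and stage of the disease". It gives no formula and no scale for the change.
- *Data collection and management (2.5.1)* records at enrolment "viral load (in copies/mL"), and at delivery the latest "viral load (done within the last 6 weeks of delivery"). No log scale is mentioned anywhere in the protocol.
- *Statistical analyses (2.8)* compares continuous variables by t test "or the Mann-Whitney *U* test (skewed data"). No transformation is named. For adjustment it says "A series of multivariable analyses using binary logistic regression model will also be carried out", which needs a yes/no outcome.
- *Standard prenatal care (2.4)*: "All women will also be commenced on ART at some point during their follow-up". Section 2.5.1 also records "type and duration of ART use (in months") at enrolment, so some women may already be treated. The share is not given.
- *Sample size (2.7.1)* sets 180 women "to detect an effect size of 0.3 of selenium supplementation on the major secondary endpoint", HIV disease progression. The unit of the 0.3 is not stated.

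**The concern.** Put together, the recording unit, the word change and the stated handling of skew lead an analyst who follows the text to subtract baseline from delivery viral load in copies/mL and rank the results. Viral load moves multiplicatively, so that difference mainly reflects how high a woman started. After a large fall on ART it is almost exactly minus her baseline value. Randomisation balances baseline between arms, so little treatment signal remains.

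At stake is the interpretation of a null result. It could be reported as no effect of selenium on viral load when it came from the scale. False-positive risk is not the issue: in a null simulation the type I error was 4.7% on the raw scale and 4.4% on log10.

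**Working it through.** **1. The plan's own figure.** (1.96 + 1.64)² / 0.3² = 12.96 / 0.09 = 144, and 144 / (1 − 0.20) = 180. The stated N is reproduced from a unitless 0.3 and contains no viral-load quantity. Evaluable women per arm: 90 × 0.80 = 72.

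**2. Ordering, by hand** (illustrative records; no distribution is assumed).

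| Record | Baseline → delivery (copies/mL) | Raw change | log10 change |
|---|---|---|---|
| A | 100,000 → 50,000 | −50,000 | −0.30 |
| B | 5,000 → 50 | −4,950 | −2.0 |
| C | 500 → 50,000 | +49,500 | +2.0 |
| D | 150,000 → 199,500 | +49,500 | +0.12 |

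The raw score puts a 2-fold fall (A) far ahead of a 100-fold fall (B), and ties a 100-fold rise (C) with a trivial one (D). Mann-Whitney is unchanged by taking logs of a single value. It is not unchanged when a difference is taken first.

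**3. Power, first set of assumptions.** The protocol gives no viral-load distribution, so all of these are assumed: viraemic baseline log10 mean 4.0, SD 0.9; floor 50 copies/mL; fall on ART 1.5 log10, SD 0.8; 72 per arm; 2,000 simulated trials per row. MW is Mann-Whitney.

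| Scenario (true extra fall) | Raw t | Raw MW | log10 change t | log10 change MW |
|---|---|---|---|---|
| All viraemic, start ART (0.3) | 3% | 6% | 45% | 44% |
| Same (0.5) | 3% | 8% | 82% | 79% |
| 30% suppressed at entry (0.5) | 2% | 6% | 32% | 31% |
| 60% suppressed at entry (0.5) | 3% | 6% | 14% | 10% |
| No ART fall, within-woman SD 0.4 (0.3) | 25% | 91% | 99% | 99% |

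The Spearman correlation of raw change with baseline is about −0.95 in the four ART rows and about −0.27 with no fall. About 10% of the women (14 of 144) carry 94% to 97% of the variance of the raw change. Repeat runs gave raw Mann-Whitney power of 5% to 8% in the ART rows.

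**4. Power, second set of assumptions.** Untreated baseline log10 mean 4.2, SD 0.9; SD of log10 change 0.8; true effect 0.5 log10 unless stated; 72 per arm; 2,000 trials per row. ANCOVA is delivery log10 adjusted for baseline log10.

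| Scenario | Raw MW | log10 change MW | log10 ANCOVA | Raw change vs baseline |
|---|---|---|---|---|
| All start ART, mean fall 2 log10 | 5% | 95% | 95% | −0.99 |
| Same, limit 20 copies/mL | 5% | 82% | 89% | −0.99 |
| Same, no limit, effect 0.24 | 5% | 41% | 42% | −0.99 |
| Mean fall 1 log10 | 18% | 95% | 96% | −0.85 |
| Half start ART, half suppressed | 17% | 46% | 88% | −0.91 |
| 20% start ART | 70% | 81% | 94% | −0.67 |
| No mean change | 81% | 96% | 97% | −0.25 |

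**5. Log10 change alone is not enough.** In a mixed population log10 change also follows baseline, because suppressed women cannot fall further. Under the first set the correlation is −0.76 with 30% suppressed and −0.92 with 60%; under the second set it is −0.82 with half suppressed. With 30% and 60% suppressed under the first set, baseline-adjusted log10 has 68% and 46% power, against 31% and 10% to 12% for Mann-Whitney on log10 change.

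**The case against.** The strongest reply is that no raw-difference rule is written down. Copies/mL is a recording unit on the enrolment questionnaire, section 2.6 says only change, and section 2.8 is a general menu of tests that does not forbid a transformation. The text is a condensed article, and a separate analysis plan could set log10. A yes/no progression outcome, in keeping with the logistic models, would also fit the wording, and up or down is the same on either scale. So would a comparison of delivery values by Mann-Whitney, which a log transform does not affect: under the first assumptions (0.5 log10, none suppressed) it has 67% power against 7% for raw change.

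This stands as a limit on the claim. A reader might infer that the protocol mandates arithmetic differences; it does not. But the text does name the unit, the change and the handling of skew, and followed as written they lead to the poor analysis.

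A reader might also infer that the endpoint always ranks women by baseline, or that the 180 rests on this scale. Neither is supported. The first needs many women starting ART on study. The treatment records taken at enrolment and the established clinic care described in *Study design and setting* (2.1) leave that share open. As for the second, the 0.3 is unitless and not tied to viral load. If it is a standardised two-arm difference, power with 72 per arm is only about 44% even on a good scale, so a null would be weak evidence in any case.

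**Conclusion.** The point holds in a limited form. The only scale given is copies/mL and the only stated remedy for skew is a rank test. Read literally, the plan tests raw differences, and the rank test does not correct their ordering; that part is arithmetic. The loss of power depends on assumed distributions and on the ART mix. It is near total (about 5% to 8% power) if most women start ART on study with falls of 1.5 to 2 log10. It is small to moderate if viral load is stable on average (91% against 99% in one set, 81% against 96% in the other). Viral load is one of three components of a secondary endpoint, and the primary endpoints are untouched. The change is still worth making before unblinding, because it is cheap and otherwise a null viral-load result could not be interpreted.

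**What to change.** - **2.6:** define the viral-load component on the log10 copies/mL scale, with one pre-stated value for any result below the assay limit (for example, the limit itself).
- **2.8:** compare the arms on delivery log10 viral load adjusted for baseline log10 viral load (ANCOVA). If many results are undetectable, add as a supporting analysis either the proportion below the limit at delivery or a censored (Tobit) model. State that differences in copies/mL will not be tested.

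Baseline adjustment is part of the fix, not an option, for the reason in step 5 of the working.

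Cost: a few sentences in two sections and one transformation in the analysis file. Both viral loads are already collected, so there are no new visits, samples or participants. The small downside is that results are reported as log10 or fold change, and the value for undetectable results must be chosen in advance.

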### Statistical methods

2.7

#### Sample size

2.7.1

Using the data from our previous study,^[11]^ we propose to enrol 148 participants in the study to investigate the effect of selenium supplementation on the primary endpoints. The study is powered for a 2-sided test with a Type I error rate of 5% and 95% power, that is, Z_α_ = 1.96 and Z_β_ = 1.64, adjusted for a 20% drop-out rate. We also propose to enrol 180 participants to detect an effect size of 0.3 of selenium supplementation on the major secondary endpoint (reduction in HIV disease progression). This is powered for a 2-sided test with a Type I error rate of 5% and 80% power, that is, Z_α_ = 1.96 and Z_β_ = 1.64, adjusted for a 20% drop-out rate. Therefore, a total sample size of 180 is used in this study with 90 HIV-infected women randomised into each of the trial arms to assess the effects of selenium supplementation on the primary and secondary outcome variables.

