### Randomisation and blinding schedule

2.3

Eligible women will be invited to give consent for participation in the trial within 2 weeks of screening. At enrolment, participants will be randomly assigned by a trained research assistant into 2 arms to receive daily oral tablet of 200 μg elemental selenium (arm I) or placebo (arm II) till their delivery using a 1:1 block randomisation code to be generated from Random Allocation software version 1.0 (May 2004) by the study Statistician. The proposed dose of selenium is one-half of the safe and tolerable upper intake level of 400 μg/day for pregnant women.^[18]^ The active drug (selenium) and placebo tablets will be indistinguishable in shape, size, and colour and will be packed in identical coded transparent dispensing sachets by the onsite pharmacy technician who will then store the coded randomization list in a sealed opaque envelope that will be kept in a locked file cabinet at the study site until the end of the study. Twelve (12) dispensing sachets with identical numeric regimen code, containing the same intervention drug will be prepared for each of the participants. At every 2-weekly follow-up visit, a new dispensing sachet with the same numeric code, containing 16 tablets of the same intervention drugs will be given to each woman and pills remaining in used sachets will be counted to assess compliance. In addition, all the women will receive the standard prenatal care (see below). Study investigators and participants will be blinded to the treatment arms until after the final analysis. The onsite pharmacy technician is not involved in the design, conduct, statistical analysis, and reporting of study findings.

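### The 180-woman sample size is stated as 80% power but was computed with the 95% Z value, and the effect size of 0.3 has no defined scale, so the true power is anywhere from about 43% to about 95%

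*Protocol article*

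**What the plan says.** The Sample size section (2.7.1) makes two calculations. The primary endpoints need 148 women, with the inputs given as "95% power, that is, Z_α_ = 1.96 and Z_β_ = 1.64". The second calculation is for HIV progression: "We also propose to enrol 180 participants to detect an effect size of 0.3 of selenium supplementation on the major secondary endpoint". The power claim follows: "This is powered for a 2-sided test with a Type I error rate of 5% and 80% power". Its inputs are given as "80% power, that is, Z_α_ = 1.96 and Z_β_ = 1.64, adjusted for a 20% drop-out rate". The larger number then governs the trial: "a total sample size of 180 is used in this study with 90 HIV-infected women randomised into each of the trial arms".

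The endpoint is defined under Confirmatory outcome variables (2.6) as "HIV disease progression (change in CD4 + cells count, viral load and stage of the disease", which is two continuous measures and one categorical one. Allocation is to two parallel arms, "using a 1:1 block randomisation code". Statistical analyses (2.8) lists t tests or Mann-Whitney for continuous data, chi-square or Fisher for categorical data, and binary logistic regression. No formula is named for the 180, and no SD, event rate or metric is given for the 0.3.

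**The concern.** One Z_beta, 1.64, is labelled 95% power for the primary endpoints and 80% power for HIV progression. Only one label can be right, and the text does not show which one produced the 180.

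The second difficulty is the undefined 0.3. Beside an endpoint made largely of changes in CD4 count and viral load, a bare effect size reads most naturally as a difference in means divided by an SD. On that reading the arithmetic behind 180 is too small for two independent arms.

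The step from 148 to 180 rests wholly on this calculation, and HIV progression is half of the aim given in the Discussion. If the true power is far below 80%, a null CD4 or viral-load result could be taken as evidence of no effect from an adequately powered comparison. If it is near 95%, the article understates its own design. A reader cannot tell which applies.

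**Working it through.** **Inputs.** From section 2.7.1: effect size 0.3, two-sided 5% (Z_alpha = 1.96), stated power 80%, printed Z_beta 1.64, drop-out 20%, total 180 (90 per arm). From section 2.3: 1:1 allocation. Evaluable after drop-out: 180 × 0.8 = 144, or 72 per arm.

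**1. Reproduce the 180.**
- Printed values: (1.96 + 1.64)² / 0.3² = 12.96 / 0.09 = 144; 144 / 0.8 = 180. Exact match.
- Stated power (Z_beta = 0.84): (1.96 + 0.84)² / 0.09 = 7.84 / 0.09 = 87.1; 87.1 / 0.8 = 108.9, so 109. No match.

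Z_beta = 1.64 corresponds to 94.9% power. The 180 was computed with the 95% value.

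**2. Reading A: 0.3 is a standardised mean difference d between arms.** For means, (Z_alpha + Z_beta)² / d² is the one-sample or paired size. Two independent arms need 2 × (Z_alpha + Z_beta)² / d² per arm, four times the total.
- Power at 72 per arm: Φ(0.3 × √(72/2) − 1.96) = Φ(1.80 − 1.96) = Φ(−0.16) = 43.6%; noncentral t gives 43.2%.
- Power at 90 per arm (no drop-out): 52.1%; noncentral t 51.7%.
- Size for 80% power at d = 0.3: 2 × 7.84 / 0.09 = 174.2, so 175 per arm, 350 evaluable, 350 / 0.8 = 437.5, so 438 enrolled (t test: 176 per arm, 352, 440 enrolled).
- Difference detectable at 80% with 72 per arm: (1.96 + 0.84) × √(2/72) = 0.47.

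**3. Reading B: Cohen's w (phi) for a 2 × 2 table.** N = (Z_alpha + Z_beta)² / w² is then a correct two-arm total. With 144 women: Φ(0.3 × √144 − 1.96) = Φ(1.64) = 94.9%.

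**4. Reading C: Cohen's f for two group means.** f = 0.3 is d = 0.6. Per arm 2 × 12.96 / 0.36 = 72, total 144. Power at 72 per arm is 95.0% (normal) or 94.7% (t test).

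**5. Reading D: absolute risk difference of 0.30 near 50%.** Per arm 2 × 0.25 × 12.96 / 0.09 = 72, total 144. For 65% against 35%, power at 72 per arm is 95.7%.

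| Scale of 0.3 | Power at 72 per arm | Stated |
|---|---|---|
| Standardised mean difference | about 43% | 80% |
| Cohen's w | about 95% | 80% |
| Cohen's f | about 95% | 80% |
| Risk difference near 50% | about 96% | 80% |

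**The case against.** A reader might infer that the authors used a one-sample formula by mistake and that the trial simply has 43% power. The article does not support that as a fact. It names no formula, and readings B, C and D reach the same 144 and 180 as correct two-arm totals, so the exact match cannot identify the formula. The continuous components do not settle it either, because Cohen's f is a scale for means. A proportion-progressing reading also has support in the text: disease stage is categorical, the Introduction speaks of a progression rate, the sample size is framed as a reduction in progression, and section 2.8 plans chi-square tests and logistic regression. This objection stands, and the 43% must be conditional.

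Nor can one say that no reading at all gives 80%. Section 2.8 mentions the paired t test, and a paired test of within-arm change at 0.3 has 80.4% power with 90 women. That is not a comparison between arms, and it ignores the planned drop-out (71% with 72 women), so it does not justify the 180. Baseline adjustment could also raise the power under reading A. If the 0.3 is in SDs of the unadjusted outcome, it would be 55% at a baseline correlation of 0.5, 71% at 0.7 and 85% at 0.8. Section 2.8 names no such adjustment for continuous outcomes.

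Finally, the primary endpoints have their own calculation of 148, so this error does not by itself undermine their sizing. None of these arguments removes the conflict between 80% and 1.64.

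**Conclusion.** Wrong as written. Independently of any interpretation, the stated 80% power contradicts the printed Z_beta, and the 180 follows from the 95% value (109 would follow from 80% in the same formula).

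The size of the consequence depends on a scale that the article does not give. It is about 43% power (52% without drop-out) if 0.3 is a between-arm standardised mean difference tested without baseline adjustment, and about 95% if it is Cohen's w, Cohen's f or a risk difference of about 0.30 near 50%. The first is the natural reading for CD4 and viral-load change but is not established. All of these figures assume 72 evaluable women per arm and a two-sided 5% test.

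**What to change.** Keep N = 180 and rewrite the paragraph in this order:

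1. Name the progression variable that the calculation concerns, and the scale of the 0.3.
2. Give the formula, and make the stated power and Z_beta agree.
3. Restate the power for that scale with 144 evaluable women, 72 per arm.

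If the scale is a standardised mean difference, the text should say that the trial has 80% power for a between-arm difference of 0.47 SD and about 43% for 0.3, and should stop describing the trial as powered for 0.3. If it is Cohen's w, Cohen's f or a risk difference near 50%, it should say about 95%. The scale has to be settled first, because either sentence would be false under the other reading.

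The cost is one paragraph and no extra participants. The downside is that the stated power or detectable effect may become less favourable.
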